### Randomization

We will randomly allocate eligible women to one of two parallel groups (experimental and control) in a 1:1 ratio according to a computer-generated random sequence. An independent statistician will prepare a set of sequentially numbered opaque sealed envelopes of the allocation group according to the generated random sequence to preserve randomization concealment. A participant’s group allocation will be revealed after verifying that the inclusion/exclusion criteria are met, and after written consent is obtained on the first day postpartum. This will avoid any selection bias introduced by the investigator knowing the allocation of the next subject.

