### Sample size

Based on data from a previous breastfeeding clinical trial that we conducted, 45% of women continue to breastfeed exclusively for 1 month postpartum [21]. We hypothesize that in women with inverted nipples, 40% of the experimental group and 5% of the control group will be exclusively breastfeeding at 1 month. To have 90% power and 5% type I error, and using the online calculator available at http://powerandsamplesize.com/Calculators/Compare-2-Proportions/2-Sample-Equality, we will need 25 women in each group to detect this 35% difference in the exclusive breastfeeding rates between the two groups.

In our recent breastfeeding support trial [21], the attrition rate was 40%. Since women with inverted nipples face more difficulties in breastfeeding than women with normally everted nipples, we hypothesize that 50% attrition rate would be a reasonable assumption for the proposed study. To account for a potential attrition rate of 50%, we inflated the sample size to become 100 women in total.

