### Statistical methods

We will compare continuous variables using Student’s *t* test and categorical variables using Chi square test. Non-parametric tests will be used to analyze variables with skewed distribution or when the number of analyzed subjects is less than 30. We will calculate the crude rates of exclusive breastfeeding and mixed feeding at 1, 3, and 6 months in both groups. The 95% confidence intervals for the crude rates of breastfeeding will be computed using the normal approximation to the binomial distribution. We will also conduct multivariable logistic regression analysis to investigate the association between exclusive breastfeeding at 1 month (dependent variable) and the use of the inverted syringe (predictor) adjusting for potential confounders such as the grade of inverted nipple. Missing data will be imputed using last observation carried forward for the breastfeeding outcomes at 1, 3, and 6 months if breastfeeding was discontinued on last follow-up, the average value for continuous variables, and random replacement to maintain proportions for categorical variables, as appropriate. We will conduct sensitivity analysis with and without the imputed missing data to assess the impact of missing data on the primary outcome. We will also conduct repeated measurement analyses using generalized estimating equations (GEE) to explore the effect of the intervention over time. Blinded, intention to treat analysis will be conducted using the Statistical Package for Social Sciences (SPSS) version 24. A *p* value of < 0.05 will indicate statistical significance.

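### Missing values are filled once and analysed as observed, with up to 50% attrition planned: within-arm filling inflates type I error, pooled filling halves the effect

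*Protocol article*

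**What the plan says.** The Statistical methods section of the protocol article gives three rules for missing data. Breastfeeding outcomes at 1, 3 and 6 months are carried forward from the last observation, on condition that breastfeeding had stopped by then. Other data are filled with "the average value for continuous variables, and random replacement to maintain proportions for categorical variables, as appropriate". The text does not say whether averages and proportions are taken within each arm or over both arms, and it mentions neither multiple imputation nor any variance correction. Significance is judged by the usual threshold: a *p* "value of < 0.05 will indicate statistical significance".

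The section also plans a "sensitivity analysis with and without the imputed missing data to assess the impact of missing data on the primary outcome". It does not say which of the two versions is the main analysis.

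On the amount of missing data, the Sample size section reports 40% attrition in the investigators' earlier trial and then raises the figure: "Since women with inverted nipples face more difficulties in breastfeeding than women with normally everted nipples, we hypothesize that 50% attrition rate would be" reasonable. The 25 women needed per group become 50, or 100 in total.

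**The concern.** A value filled in once and then analysed as real adds apparent sample size but no information. With a few percent missing this hardly matters. Here the plan allows for half. The sample size calculation rests on 25 evaluable women per arm, so filling back to 50 claims precision that the same document expects not to have.

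The harm depends on a choice left open. Filling within arm preserves the observed difference but understates its standard error, so false positives rise. Filling from both arms pooled pulls the arms together, so a real effect shrinks.

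Two further gaps bear on the primary outcome:

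- The endpoint is exclusive breastfeeding, but the carry-forward condition refers to having stopped breastfeeding. Read literally, a woman already giving artificial milk at last contact is not covered. She would fall to random replacement and could be counted as exclusively breastfeeding.
- The Sample size section ties the higher attrition to breastfeeding difficulty, so loss may depend on the outcome. Neither planned version varies what is assumed about women lost with unknown status.

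**Working it through.** **Inputs.** From Sample size: "To have 90% power and 5% type I error"; "40% of the experimental group and 5% of the control group will be exclusively breastfeeding at 1 month"; "we will need 25 women in each group to detect this 35% difference"; attrition 50%, and 40% in the earlier trial. From Randomization: 1:1 allocation, so 50 per arm.

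**The plan's own figure.** Unpooled two-sided formula: n = [0.40×0.60 + 0.05×0.95] × ((1.960 + 1.282)/0.35)² = 24.66, so 25 per arm. Then 25/(1 − 0.5) = 50 per arm, 100 in total. The stated sample size reproduces.

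**Random replacement within arm.** Take n = 50 and k = 25 observed. The variance of the filled proportion is p(1−p)[1/k + (n−k)(1−1/k)/n²] = p(1−p)[0.04 + 0.0096] = 0.0496 p(1−p). The chi-square test assumes p(1−p)/50 = 0.02 p(1−p). The ratio is 2.48 and its square root 1.575, so the real type I error is about 2Φ(−1.96/1.575) = 2Φ(−1.244) = 21%. Simulation with a random number lost per arm (200,000 trials per scenario) gives 20.2% at a true rate of 5%, 23.3% at 20%, and 22.9% at 22.5% and at 40%. If replacement reproduces the observed proportion exactly, the figure is 18-20%.

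**Mean fill within arm.** The filled variance is (k−1)/(n−1) = 24/49 = 0.490 of the true one, and n is counted as 50 instead of 25. Assumed over true standard error = √(0.490×25/50) = 0.495, so type I error is about 2Φ(−1.96×0.495) = 2Φ(−0.970) = 33%. Simulation (100,000 trials, t test) gives 33.2%.

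**Pooled fill.** The expected difference is (1 − 0.5)×35 = 17.5 points. Simulation gives 17.3 points and 57% power. A mean difference of 1.0 SD becomes 0.50 SD. Type I error is 3.6-5.3% for random replacement (below 1% with exact proportions) and 5.0% for means.

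**Observed cases only, same setting.** Type I error 2-5%, difference 35 points, power 89%.

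**Primary outcome with partial carry-forward.** True rate 22.5% in both arms, 50% missing, within-arm filling. A share of the missing values is randomly replaced and the rest set to failure:

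| Share randomly replaced | Type I error |
|---|---|
| none | 5.2% |
| a quarter | 10.2% |
| half | 14.8% |
| three quarters | 19.1% |
| all | 22.9% |

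**Less missing data.**

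| Missing | Random replacement, within arm | Mean fill, within arm | Pooled fill |
|---|---|---|---|
| 40% | 15.7-18.3% | 24.0% | 35 points becomes 20.8; 1.0 SD becomes 0.60 |
| 20% | 8.9-10.9% | not run | not run |
| 10% | 6.3-7.8% | not run | not run |

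All simulations assume data missing completely at random. Any bias from outcome-related loss would be additional.

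**The case against.** The strongest reply is that random replacement may not touch the primary outcome. The breastfeeding outcomes have a rule of their own, and random replacement could be meant for other categorical variables. The wording allows this. But then the plan has no rule for a woman lost before 1 month while still breastfeeding, so the text needs repair on either reading. Likewise, the carry-forward condition may be meant to include loss of exclusivity; it does not say so.

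Second, the observed-case version keeps type I error at 2-5% and power at 89% when loss is random, so comparing it with the imputed version would expose part of the problem. This stands for the primary outcome. The comparison is not planned for secondary outcomes, and the main version is not named.

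Several stronger readings are tempting but not supported:

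- *A false-positive rate of 20-33% for the primary test.* The 33% belongs to continuous secondary scores only. The 20-23% is an upper value, because carry-forward sets known discontinuers to failure, and pooled filling does not inflate the rate.
- *Half of each outcome will be missing.* The 50% is a planning allowance not tied to any visit. Satisfaction is measured at 1 week, where so large a loss would be surprising.
- *Both planned analyses assume that loss is unrelated to outcome.* Carrying discontinuation forward is outcome-related handling, though partial.
- *Informative loss is shown to create an effect.* With 20% exclusive in both arms (10 of 50) and only non-exclusive feeders lost, 40% against 50% attrition gives 10/30 = 33% against 10/25 = 40%. That is a spurious gap, but z is about 0.5 (p about 0.6), and the example ignores carry-forward. That loss depends on the outcome is a reasonable inference from the Sample size section, not a stated fact.

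**Conclusion.** The point holds in conditional form. The protocol states a single-imputation method that works badly at its own planning level of attrition, whichever way the open choice is read. With 50% missing completely at random and 50 per arm, within-arm filling gives a type I error of about 20-23% for binary outcomes and 33% for continuous secondary scores. Pooled filling keeps the error near 5% but reduces 35 points to about 17 and power to about 57%. For the primary outcome, 10-19% is the within-arm range when a quarter to three quarters of the missing values are randomly replaced. That share is an assumption, since the protocol does not give it. The distortion shrinks as attrition falls.

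Separately, the literal carry-forward condition leaves out women already giving artificial milk, and the sensitivity analysis does not test assumptions about women lost with unknown status.

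**What to change.** 1. Delete mean imputation and random replacement for outcomes.
2. Score exclusive breastfeeding as not met for any woman with artificial milk or discontinuation recorded before loss.
3. For outcomes still missing, use multiple imputation with Rubin's rules, or analyse observed cases, and name which is the main analysis. The imputation model should contain treatment arm and a few collected predictors, for example grade of inversion, previous breastfeeding and day-1 feeding. Day-7 feeding is not suitable: the Data collection section lists only reminders, the breastfeeding evaluation and questions for that call, and the diary comes in at the 30 to 40 day visit.
4. Use an imputation method that copes with sparse events. At a 5% control rate, 25 observed controls yield 25×0.05 = 1.25 expected events, with a 0.95^25 = 28% chance of none.
5. Add two sensitivity analyses for the primary outcome: missing counted as not exclusive in both arms, and a tipping-point analysis that varies the rate among missing women by arm.
6. Use multiple imputation or observed cases for satisfaction and quality of life.

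The cost is wording, some extra analyst time and wider intervals. The missing-equals-failure analysis is itself severe: if half are lost at random, the 35-point difference becomes 0.5×35 = 17.5 points (simulated power 85%). It belongs among the sensitivity analyses.

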### Ethics approval

This study is approved by the Institutional Review Board (IRB) of the American University of Beirut. Written informed consent will be obtained from all participants. Since the study involves using the inverted syringe technique and documentation of relevant data in a diary, we estimate that the risks to women from participating in this study are negligible, not exceeding those of current standard practice. The only risk from nipple manipulation in the experimental group is the rare possibility of uterine contractions and labor induction if done prior to delivery. Since participants will start using the syringe right after delivery, this risk is eliminated. We also anticipate that the use of the syringe will result in less pain and less sore or bleeding nipples in the experimental group compared to the control group, who are at much greater risk for these complications secondary to poor infant latch. We will collect information on any adverse events during follow-up of participants, and will report all adverse events to the IRB as per institutional policies. Should any adverse events result directly from this study, the investigators’ institution will cover the cost of treating, on its premises, those medical adverse events.

Confidentiality of participants will be secured by storing the hard copies of the data collection forms in locked cabinets in the principal investigator’s office (MN). Access to electronic data stored in the SPSS data file will be password-protected, and restricted to the principal investigator (MN). The blinded analyst will be provided with a de-identified dataset to preserve confidentiality. Data will be stored for 5 years after publication of the study findings.

We will report any important modifications of the protocol to the IRB, trial participants, and trial registry. The trial’s results will be disseminated to healthcare professionals and the public through publication in a refereed journal, trial registry, and medical conferences.

## Discussion

This trial aims to investigate breastfeeding success with the use of the inverted syringe technique in women with grade 1 or 2 inverted nipples. We anticipate that this technique will increase the rates of direct infant latch on mother’s breast and exclusive and any breastfeeding continuation, will reduce maternal breastfeeding-associated complications such as sore or bleeding nipples, breast engorgement, or mastitis, and will improve maternal satisfaction with breastfeeding and maternal quality of life.

The main strength of our study is its design, as it will be the first trial to investigate the effectiveness of the inverted syringe in breastfeeding women with inverted nipples. However, it may be limited by its open-label status, which may increase the risks of performance and detection biases. Given the nature of the intervention, it would be difficult to blind the participants. Although the sample size is only 100 women, the study is powered to detect the hypothesized 35% difference in 1-month exclusive breastfeeding rates between the two groups, taking into account a potential high attrition rate. Another limitation is the fact that the study is conducted in a single center, which may impact its generalizability. However, women with inverted nipples face similar problems, irrespective of the context. Also, the intervention is readily available to women everywhere and is affordable. If the findings of this trial are positive, then replication of the study will still be needed in other contexts.

### Trial status

This is the first version of the study protocol dated May 8, 2018, the day it received approval from the IRB. Participant recruitment began on June 7, 2018 and is expected to be completed in 2 years.

## Data Availability

The de-identified dataset will be stored in a public data repository for future data sharing.

## Abbreviations

MR/MCA: Mental retardation/multiple congenital anomalies
SPSS: Statistical Package for Social Sciences
